Where participants screening data is assessed as making them eligible, participants will be randomised to either a standard care control group, or standard care plus 3 sessions of IE per week intervention group. Participants will be randomised in a 1:1 ratio using pseudo-random numbers. Random permuted blocks will be used within stratification to conceal the sequence of treatments and ensure that treatments are balanced at the end of every strata block. Stratified randomisation will ensure balanced groups based on age (≤50, >50 years), biological sex at birth (male, female), and treatment status (hypertension medication, no hypertension medication), giving 8 strata in total. Participants will be allocated using an online data capture software (see data management section).

As an exercise intervention study, participants will not be blinded to their group allocation. An independent statistician was employed to ensure that the study statistician will be blinded to randomisation allocations and will only analyse unidentifiable data. Data will only be unblinded in the case of serious adverse events (see page 13–14) and for the Chief Investigators only. The study statistician will not receive the 12-month data until the main study data has been analysed, and treatment allocation revealed. At the end of the study, all participants will have access to the IE exercise programme content, including control participants should they wish to try the IE programme and as an incentive to continue as a control in the study until then.

**
*Study Intervention*
**

The participant’s normal care provider (GP or hospital where appropriate) will retain responsibility for the participant’s healthcare outside the research study. On completion of the baseline data collection (see Participant timeline and assessments below), participants will be provided with access to relevant intervention and/or standard care resources within the study website portal and via email. The resources will also include an overview of the timepoints, data collection and training for specific measurements (such as blood pressure monitoring). There will be a dedicated telephone support line during office hours. Participants will be encouraged to continue their normal activities during the study.

**
*Standard care advice – healthy lifestyle – all participants*
**

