The primary outcome, change from baseline in systolic BP at 3-months, will be analysed using analysis of covariance, with a fixed treatment effect allowing adjustments for baseline values, sex, age, and hypertension medication status. The primary analysis will be conducted using an intention to treat approach with a two-sided 5% significance level. Secondary analysis will examine treatment effects under different scenarios for compliance with allocation/treatment, using per protocol approaches. Prior to analysis distributional assumptions will be assessed, and the data may be transformed or alternative nonparametric approaches used where there is evidence of non-normality. Data from the IE experience questionnaires will be analysed using descriptive statistics, as will secondary process outcomes such as recruitment and adherence rates, attrition and completeness of the data.

We will undertake an interim analysis of the first 50 participants’ fourth bout RPE scores and the extent to which these are in range of the target zone to check intervention fidelity to determine the extent to which the intervention is being delivered as intended. Data collected for this purpose involves confirmation from participants on whether they altered their wall squat height and whether their RPE was outside of range.

To avoid loss of efficiency, missing outcome values (both primary systolic blood pressure and secondary diastolic blood pressure) will be imputed using multiple imputation, if the proportion of missing data is greater than 5% and less than 40%.
^41^ Where there are less than 5% missing data, the proportion of missing data is considered negligible and missing observations will be excluded. Multiple imputation methods perform less well when the amount of missing data is substantial, if more than 40% of the primary outcome data are missing in the primary analysis the assumptions are less plausible. The interpretative limitations of the trial data will be discussed in the results section, where this is the case.

An imputation model containing all potential prognostic baseline covariates, the primary outcome variable at 4 weeks follow-up, and the secondary outcome variable diastolic blood pressure at 4 weeks follow-up will be used.
^42^ The number of imputations will be dependent on the amount of missing data, as a minimum the number of imputations will be derived to ensure at least 96% statistical efficiency (RE) according to the formula below, where

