We will conduct a cost consequence analysis and present evidence on a range of costs and outcomes associated with the intervention. We will present the number and percentage of participants with missing values for each cost element and each outcome measure. Data from the QOL and economic questionnaires will be transferred to STATA 18 and analysed using descriptive statistics. We will estimate the mean and 95% confidence intervals for each type of cost (intervention, NHS primary care, NHS secondary care), and the difference between intervention and control group. We will calculate the mean QOL and 95% confidence intervals for both groups both unadjusted and after adjusting for baseline utilities and we will estimate the difference between the two groups. We will also estimate the QALYs for each group at 3-months and 6-months.

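### The quality-of-life comparison adjusts for baseline utility at most and omits the three stratification factors, so its intervals may be slightly wider than necessary (minor)

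*Protocol article*

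**What the plan says.** Four places in the protocol article bear on this.

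- **Participant enrolment, Randomisation.** "Stratified randomisation will ensure balanced groups based on age (≤50, >50 years), biological sex at birth (male, female), and treatment status". This gives eight strata, with random permuted blocks within them.
- **Statistical methods, Quantitative data analysis.** The primary outcome is analysed by "analysis of covariance, with a fixed treatment effect allowing adjustments for baseline values, sex, age, and hypertension medication status". All three stratification factors are therefore in the primary model.
- **Statistical methods, Health economic analyses, quality of life.** "We will calculate the mean QOL and 95% confidence intervals for both groups both unadjusted and after adjusting for baseline utilities". A difference between the two groups is also to be estimated. No covariate other than baseline utility is named.
- **Same section, costs.** "We will estimate the mean and 95% confidence intervals for each type of cost (intervention, NHS primary care, NHS secondary care), and the difference" between the groups is planned. No adjustment is stated either way.

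Table 1 schedules the quality-of-life questionnaire at baseline, month 3 and month 6. The health resource use questionnaire appears only at months 3 and 6, so baseline utility is collected but baseline resource use is not.

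**The concern.** When allocation is balanced within strata, differences between strata contribute little or nothing to the true sampling error of the between-arm difference. A model that ignores the strata leaves that variance in its residual, so its standard error overstates the real uncertainty. The usual remedy is to include the stratification factors as covariates, as the primary analysis does here.

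For quality of life the article states a narrower set. This is a choice on the page, not a gap. At stake is some precision in the utility differences that feed a cost consequence analysis, which is a secondary objective meant to inform commissioning. The validity of any conclusion is not at stake.

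**Working it through.** **Sample size used.** Under Sample size the article gives a difference of 5 mmHg, SD 14.4, 90% power and 5% significance. The normal approximation gives 2 × 14.4² × (1.960 + 1.282)² / 5² = 174.3, so 175 per arm. The t-based calculation gives 176 per arm, 352 in total (power 0.901), and 352 / 0.65 = 541.5, so 542 randomised. The stated figures reproduce. They concern systolic BP only; the article gives no SD or precision target for utility or cost.

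**Formula.** Let r be the share of the variance left by the planned model that the three factors explain. Then:

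- width with the factors / width without = √(1 − r)
- coverage of the nominal 95% interval without the factors, if balance is kept = 2Φ(1.96/√(1 − r)) − 1

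The article gives no value of r, so both readings below are assumptions.

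**Reading A: the factors explain 5%, 10% or 20% of the variance left after baseline utility.**

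| r | √(1 − r) | Interval narrows by | Coverage without the factors |
|---|---|---|---|
| 0 | 1.000 | 0% | 95.0% |
| 0.05 | 0.975 | 2.5% | 95.6% |
| 0.10 | 0.949 | 5.1% | 96.1% |
| 0.20 | 0.894 | 10.6% | 97.2% |

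A simulation agrees. It used 542 randomised, eight strata, an assumed block size of 4, 35% random loss and 4,000 trials per setting. Mean standard errors for utility fell from 0.1067 to 0.1042, from 0.1067 to 0.1014 and from 0.1068 to 0.0957, which are reductions of 2.3%, 5.0% and 10.4%. Coverage of the baseline-only interval was 95.6%, 96.1% and 96.2%. The Monte Carlo error is √(0.95 × 0.05 / 4000) = 0.34 points. Random loss disturbs the balance within strata, which is why the last coverage figure lies below the formula's 97.2%.

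**Reading B: the factors explain 5%, 10% or 20% of total variance, with baseline and follow-up utility correlated 0.6.** Here the factors act equally on baseline and follow-up, so baseline utility already carries part of their effect. With baseline alone, the residual variance is 1 − 0.6² = 0.64. With the factors added it is (1 − R²)(1 − c²), where c = (0.6 − R²)/(1 − R²).

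| R² of total | c | Residual variance with factors | √(ratio to 0.64) | Interval narrows by |
|---|---|---|---|---|
| 0.05 | 0.579 | 0.632 | 0.993 | 0.7% |
| 0.10 | 0.556 | 0.622 | 0.986 | 1.4% |
| 0.20 | 0.500 | 0.600 | 0.968 | 3.2% |

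A simulation with 352 completers and 3,000 trials per setting gave the same figures. Mean widths fell from 0.3356 to 0.3334, from 0.3355 to 0.3308 and from 0.3357 to 0.3251. With no association, the widths were 0.3354 and 0.3355. Baseline adjustment, which is already planned, narrowed the interval from 0.4188 to 0.3354, or about 20%.

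**Why the readings differ.** They define the explained share differently. In reading B the share of the remaining variance is 1 − 0.632/0.64 = 1.3%, 1 − 0.622/0.64 = 2.8% and 1 − 0.600/0.64 = 6.25%, which puts it at the low end of reading A's range.

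**The case against.** **The analysis is descriptive.** The article says "Data from the QOL and economic questionnaires will be transferred to STATA 18 and analysed using descriptive statistics", and no test, significance level or power applies to these outcomes. This lowers the importance of the point but does not remove it, because the same paragraph plans 95% confidence intervals and a between-arm difference. Those are inferential quantities and should reflect the design.

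**The intervals are too wide.** A reader might infer this as a fact. The article does not support it: nothing in it says how far age, sex or medication status predict utility. If they predict nothing beyond baseline utility, the excess width is zero.

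**The economic analysis contradicts the primary analysis.** A reader might infer this too. It does not: the ANCOVA covariates are given for systolic BP, and nowhere does the article say that utility or cost will follow the same model. The difference is one of approach.

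**The cost comparison leaves out the strata.** For costs the article is silent, and it refers to a full Data Analysis Plan that is not shown and may list covariates. The cost remark is therefore conditional. Adjusting the intervention cost has no evident purpose either, because the exercise programme is delivered in one arm only.

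**The planned method is sound.** Adjusting for baseline utility is the most valuable single step and is already planned. This stands. What remains is a small further gain in precision.

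**Conclusion.** The point holds for quality of life, as a minor one. The stated adjustment set omits three factors that define the strata and that the primary model already uses. Any resulting error is conservative: intervals somewhat too wide, with no bias and no inflated type I error from the omission itself.

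Under the assumed shares, the possible narrowing is about 2.5% to 11% on reading A and about 1% to 3% on reading B. It is nil if the factors add nothing to baseline utility. These figures rest on assumed explained variances, an assumed correlation of 0.6 in reading B, an assumed block size of 4 in the simulations, and either no loss or random loss. Dropout related to these factors and differing by arm was not examined, and nothing here rests on it.

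**What to change.** In Health economic analyses, state that the between-arm difference in utility at 3 and 6 months will be estimated from a regression on arm, baseline utility, age, sex and hypertension-medication status. Report that as the difference and keep the unadjusted group means as description.

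For NHS primary- and secondary-care costs, state that the difference will be estimated from a regression on arm and the same three factors, with robust or bootstrap standard errors, unless the Data Analysis Plan already says so. With no baseline resource use collected, these factors are the obvious predictors already in hand. Leave the intervention cost as a simple description.

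The cost is a sentence or two of text. Every covariate is already recorded for randomisation or scheduled at baseline, so no new data are needed.

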### Study governance

**
*Participant withdrawal*
**

Participants are free to withdraw at any time from the study without giving reasons and without prejudicing their further treatment. They will be made aware of this during consent and at each study timepoint. They will also be informed that data collected up to the point of withdrawal will be used unless they specifically state that they do not wish for this. The right of a participant to refuse participation without giving reasons will be respected.

**
*Trial registration*
**

The study is registered with the UK’s clinical study registry, the ISRCTN under reference number 28188474.

**
*Study sponsorship*
**

East Kent Hospitals University NHS Foundation Trust are the sponsor and are responsible for ensuring regulatory compliance, trial monitoring, safety, proper data management, and that the trial is adequately funded and concluded. Name and contact information for the trial sponsor:

East Kent Hospitals University NHS Foundation Trust.

[name].

Research & Innovation/Clinical Trials Unit Manager
[contact]

**
*Ethical approvals*
**

Ethical approval has been granted by the National Health Service Health Research Authority London - Bromley Research Ethics Committee (Reference number 24/LO/0911, IRAS number 331559). The study will be conducted in accordance with the UK Policy Framework for Health and Social Care Research March 2018
^47^ and recommendations for physicians involved in research on human subjects adopted by the 18th World Medical Assembly, Helsinki 1964 and later revisions.
^48^

**
*Protocol amendments*
**

Protocol amendments will be decided on by the project team and Chief Investigators. Full version control procedures will be adopted. Protocol amendments will be submitted and approved by the ethics committee where appropriate before being put in place.

**
*Study oversight groups*
**

The ISOFITTER study steering committee is chaired by [name] (Chair of the British and Irish Hypertension Society Collaborative Research Standing Committee). The steering committee is composed of at least 75% members who are independent to the study team. The committee includes the Chief Investigators, an independent statistician and health economist, clinicians with expertise in hypertension/clinical trials, an exercise specialist, an expert in qualitative health services research, an implementation specialist and two independent lay members. The committee critically oversees progress, outputs, deliverables and governance of the project. The delivery of the study is managed by the East Kent Clinical Trials Unit (CTU). A project management group brings together the CTU and the academic delivery team from the University of Kent and Canterbury Christ Church University. A research inclusion subcommittee, chaired by [name] [name] as a public co-applicant on the study, oversees recruitment of a representative study sample, ensuring inclusion of participant groups commonly under-represented in research such as those on low income and those from minority ethnic groups.

**
*Adverse event monitoring*
**

For the purpose of this study an adverse event (AE) is defined as any untoward medical occurrence in a study participant, whereas a serious adverse event (SAE) is any untoward medical occurrence that results in death, is life-threatening at the time of the event, requires participant hospitalisation or prolongation of existing hospitalisation, results in persistent or significant disability/incapacity, or consists of a congenital anomaly or birth defect. Other ‘important medical events’ may also be considered serious if they jeopardise the participant or require an intervention to prevent one of the above consequences. Only AEs or SAEs which might have resulted (definitely or probably) from the study intervention, e.g. muscular injury in the leg as a result of IE, will be recorded. These will be submitted by the participant in their assessment questionnaires. The CTU will monitor reported AEs from participants and report any AEs or SAEs as following standard governance processes and requirements.

Common wall squat related adverse events would be similar in nature to other forms of recommended exercise (e.g. aerobic exercise or strength training) and may include muscle soreness after exercise, stress on joints (particularly the knees and ankles), dizziness during or after exercise, blood pressure spikes if holding of breath occurs during exercise (instructions to breath normally is including in the instructions to participants) and potential post-exercise hypotension. These will be recorded throughout the study.

In the event of an Adverse Event (AE) or Serious Adverse Event (SAE) the clinical lead applicant would be unblinded to the participant’s randomisation group to allow them to assess the relatedness of the event to the intervention. This information would be available on the data collection questionnaire/forms stored centrally in the trial master file. This information would be shared by the delivery team only when necessary.

Although IE can be undertaken in pregnancy, we have decided to take a conservative approach and exclude pregnant participants. Any women of childbearing potential should agree to use a medically accepted method of contraception while they are participating in the study. Should a participant get pregnant during the study, they will be asked to notify the study team within 7 days of becoming aware of the pregnancy. In case of a pregnancy while receiving study treatment, a participant should be withdrawn from the study.

**
*Data monitoring and audit*
**

Only the CTU delivery team will have access to the full dataset throughout the study. The statistician and research team will have access to an anonymised data set for analysis. Upon completion of analysis, the anonymised data will be available to other researchers upon reasonable written request with clearly defined purpose and its use will be to benefit of the wider society (see section 7).

Study data will be collected and managed using REDCap electronic data capture tools
^49^
^,^
^50^ hosted at East Kent Clinical Trials Unit. All data will be entered on to a secure server using REDCap software. Data quality will be enhanced using range checks and prompts for missing fields. The decision not to establish a Data Monitoring Committee (DMC) for this project is because the project has been evaluated as low risk by the Sponsor’s Risk Assessment. This included an evaluation of participant safety with the interventions/procedures involved being considered to pose minimal risk to participant health and well-being, the inclusion of relatively healthy participants who are treated or untreated for hypertension, and finally the disease under study does not involve high-risk or complex conditions that would require intensive monitoring to ensure safety or efficacy. Ongoing data for this project are reported monthly to the Project Management Group to review data to support the progress of the study and to address any emerging issues or concerns. Given this structured and regular oversight, the need for a separate, external DMC is not deemed necessary.

Data will be reported on a quarterly basis to the Trial Steering Committee for review. Central/remote monitoring activities will take place monthly from first recruit onwards. Remote monitoring activities will be as follows, independent of the investigators and carried out by CTU Governance and/or Facilitator:
•informed consent completed on REDCap reviewed – first participant and 10% monthly;•investigator site file review;•training & delegation review;•informed consent process documentation for consent received over the telephone.

To protect the participants, minimal personally identifiable information will be collected. The participant will input their data directly onto the data management system REDCap. Only those members of the study team with delegated duties will have access to these data. Participants agree to share contact details with the BP machine provider and the courier who will deliver the BP monitor. Contact details held by the delivery team will be destroyed at the end of the study, retaining only participant study codes. Only non-identifiable information can be shared with the wider study team for the purpose of the project. Any personal data will be stored within REDCap software or password-protected computers within a limited access folder on the Sponsor network with unique codes allocated to each service user.

Personal data will only be shared with the university partners for the purpose of contacting participants directly about their exercise intervention or for participation in participant focus groups. Electronic files with personal information will be password protected and stored on the university partner networks in folders that can only be accessed by the research team. These folders will not be transferred from the network onto personal computers. Data in paper form will be transferred into electronic copy and destroyed as early as possible, but where it needs to be stored this will be in locked filing cabinets in offices that are locked when unoccupied. Access to the data collected during the project (including any participant personal data) will be restricted to the research team, and data will not be shared with anyone else. At the end of the study the data will be electronically archived by the sponsor and destroyed after five years.

**
*Dissemination policy*
**

Participants and stakeholders will receive an easy read summary of the results which will also be shared widely on mainstream and social media. It will also be available for use by our collaborating and other national charities and professional bodies to disseminate findings. Reporting to the funder will be 6-monthly and a final report at study completion. Publication will be in peer-reviewed journals, including an effectiveness data paper, a separate implementation contexts paper and a commentary on the approaches to representative recruitment. There will be an executive summary of study findings for providers and commissioners and healthcare local organisations. Findings will be presented at national and international conferences, e.g. European Hypertension Society and British and Irish Hypertension Society. Standard International Committee of Medical Journal Editors (ICMJE) authorship guidelines will be adhered to and there will be no use of professional writers in any publications. The IE training protocol will be made publicly available online at the end of the study.

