## Abstract

Background High blood pressure (BP) affects more than one in four adults in England and only one in three patients are being treated effectively. Treatment of high BP includes changes to lifestyle such as more physical activity and/or taking medication. However, low adoption and high attrition are common with the large amounts of exercise currently recommended (>150 minutes moderate exercise per week plus 2 strength sessions). Evidence suggests that isometric exercise (IE), holding a fixed body position for a period of time, for example a wall squat, results in greater long term BP reductions, with less time and effort, than other recommended exercise. This ISOFITTER study aims to evaluate the effectiveness of IE to help reduce BP in hypertension in a real world setting. Methods A multi-centre, randomised, controlled trial of an isometric exercise wall squat intervention for hypertension employing an effectiveness-implementation hybrid type-1 design. Adults (n = 542) with Stage 1 or Stage 2 hypertension, on no more than one antihypertensive, and no other medical contra-indications will be randomised to either a standard care plus IE intervention group or standard care control group. Blood pressure readings, fidelity measurements, medications, adverse events, quality of life, participant satisfaction and health service use will be collected at baseline, week 4, month 3 and month 6 with a subgroup (n = 50) of the IE arm invited to continue for 12 months. Qualitative participant focus groups and interviews with wider stakeholders will collect implementation data. Results The ISOFITTER study will establish effectiveness of a self-administered, home-based IE intervention in lowering blood pressure in people with uncomplicated stage 1 and 2 hypertension. Implementation evidence will support patient delivery, context for scaling up of the intervention and intervention cost. Conclusion Lifestyle changes for the treatment of hypertension in the absence of other risk factors should not be overlooked. For long term hypertension management, easily adopted, evidenced exercise interventions are needed. This study will help to address this evidence gap.

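### Adverse events are recorded only if definitely or probably caused by the intervention, so AE and SAE counts cannot be compared fairly between arms

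*Protocol article*

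**What the plan says.** Under Adverse event monitoring in Study governance, the protocol article starts from the usual broad definition: "an adverse event (AE) is defined as any untoward medical occurrence in a study participant". It defines serious events by the standard seriousness criteria. It then narrows what enters the record to "Only AEs or SAEs which might have resulted (definitely or probably) from the study intervention". The restriction is on recording, not only on expedited reporting, and it covers SAEs as well as AEs. On the route of capture it adds: "These will be submitted by the participant in their assessment questionnaires".

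The next paragraphs list expected events (muscle soreness, joint stress, dizziness, blood pressure spikes, post-exercise hypotension) and say they will be recorded throughout. The list is introduced by its link to the exercise: "Common wall squat related adverse events would be similar in nature to other forms of recommended exercise". When an AE or SAE occurs, the clinical lead is unblinded to the group "to allow them to assess the relatedness of the event to the intervention".

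Elsewhere no causal condition appears. The Abstract says "adverse events, quality of life, participant satisfaction and health service use will be collected at baseline, week 4, month 3 and month 6", and the follow-up assessment section lists adverse events among the data collected under the schedule of assessments. The Randomisation section states that "participants will not be blinded to their group allocation". Controls are offered the exercise content after their last visit (Ancillary and post-trial care).

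**The concern.** In a randomised trial the control arm shows how many events would have occurred anyway. A rule that admits an event only when the intervention is its definite or probable cause removes that information, because an arm not exposed to the intervention can hardly produce a qualifying event. The record becomes a list from the exercise arm, selected by opinion about cause.

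Two things are at stake. First, equal true risks would show up as an imbalance against the exercise, while an excess of events that nobody attributed to it would not show at all. Second, a serious event of possible or undetermined cause, such as a cardiovascular admission, need not be recorded. The exercise is unsupervised and done at home by people with clinic pressures up to 179/119 mmHg, and the training protocol is to be made public at the end of the study. Readers will want to know about harms, and events that were never captured are hard to recover later.

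**Working it through.** **1. Denominators.** The protocol states no AE or SAE rate, so there is no safety figure to reproduce. The group sizes used below do reproduce. For a 5 mmHg difference, SD 14.4, two-sided 5% and 90% power, the t-based calculation needs 176 per arm (power 0.901; 175 per arm gives 0.8996), or 352 in total. With 35% attrition, 352 / (1 − 0.35) = 541.5, rounded up to 542, or 271 per arm.

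**2. The statements side by side.**

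| Place | When is cause judged? | Does cause limit what is captured? |
|---|---|---|
| AE definition | not mentioned | no |
| Recording rule | before or at recording | yes: definite or probable only |
| Role of the clinical lead | after the event, with group revealed | no; presupposes events arrive unjudged |
| Abstract and follow-up assessments | not mentioned | no |

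Rows 2 and 3 cannot both govern. If only definitely or probably related events are recorded, the clinical lead has few unjudged events to assess. If the lead makes the judgement, capture must come first and the recording rule is wrong as written. The recording rule is also inconsistent in itself: its opening words admit any event the intervention might have caused, and its bracket then keeps only two causality grades, which leaves out possible causes.

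**3. What the rule does to each arm.** Let p be the all-cause SAE risk, equal in both arms, and q the share of exercise-arm SAEs judged definitely or probably related. Both are assumptions.

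- SAEs occurring = 542 × p
- SAEs recorded = 271 × p × q, all in the exercise arm; control = 0
- Share unrecorded = 1 − q/2

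| p | q | Occurring | Recorded (exercise) | Recorded (control) | Unrecorded |
|---|---|---|---|---|---|
| 1% | 10% | 5.4 | 0.3 | 0 | 95% |
| 1% | 50% | 5.4 | 1.4 | 0 | 75% |
| 2% | 10% | 10.8 | 0.5 | 0 | 95% |
| 2% | 50% | 10.8 | 2.7 | 0 | 75% |
| 5% | 10% | 27.1 | 1.4 | 0 | 95% |
| 5% | 50% | 27.1 | 6.8 | 0 | 75% |

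The arms have equal risk in every row, yet every recorded event is in one arm.

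**4. What full capture would buy.** With 271 per arm and assumed risks of 2% against 4% (5.4 and 10.8 events), the standard error of the difference is √(0.02 × 0.98/271 + 0.04 × 0.96/271) = 0.0146. The 95% CI is 2.0 ± 1.96 × 1.46, or −0.9 to +4.9 percentage points. Power is about 28% by the normal approximation and about 20% by Fisher's exact test. For commoner events, the normal approximation gives about 60% for 5% against 10%, and 97% for 5% against 15%.

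**5. Both-arm data that remain.** The schedule of assessments has health resource use at months 3 and 6, and the economic section compares costs by type, including NHS secondary care, between groups. That gives an indirect view of admissions. It is planned as cost and service-use data, not as an AE or SAE record.

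**The case against.** Several points on the other side are fair.

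- A reader might infer that the unblinded participant decides which events are related. The text does not say so. It says that participants submit events, and it gives the relatedness assessment to the clinical lead. The questions participants actually see are in data collection tools that are not shown. What stands is that reports come from people who know their allocation, under a rule that does not say who applies the causal test.
- A reader might infer that nothing about safety can be compared between arms. That is too strong. Health resource use, home blood pressure and concomitant medication are collected in both arms. The limitation applies to AE and SAE counts.
- The expected wall-squat events are to be recorded throughout. This helps in the exercise arm. The list is defined by its relation to the exercise, so it supplies no control count.
- A reader might take the absence of a data monitoring committee to mean that there is no second check. The protocol gives the sponsor's low-risk assessment as its reason and provides for monitoring of reported AEs by the trials unit, monthly project group review and quarterly data to a steering committee with at least 75% independent members. These bodies can, however, act only on events that were recorded.
- No between-arm safety outcome is listed under Statistical methods, and the Conclusion makes no safety claim, so no stated analysis fails. The fault lies in the data-capture rule.
- Full capture would not give a strong test. An assumed doubling from 2% to 4% would probably be missed even with perfect recording, and attrition would reduce the power further.

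Related-only handling can be defended for expedited reporting in a low-risk trial. That defence does not extend to leaving SAEs out of the record.

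**Conclusion.** The point holds as a fault in a stated rule. As written, it gives a control arm with close to no recordable events and drops serious events of possible or unclear cause, so AE and SAE counts cannot be compared fairly between arms. It also conflicts with the clinical lead's later assessment of relatedness and with the unrestricted descriptions of AE collection in the Abstract and the follow-up section.

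The direction of the bias follows from the rule and the controls' lack of access to the exercise, and needs no assumed rate. The size does: 75% to 95% of SAEs unrecorded rests on equal risks and on 10% to 50% of exercise-arm SAEs being judged definitely or probably related.

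This should be fixed. The primary outcome, the sample size and the main analysis are not affected.

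**What to change.** Reconcile the Abstract, the follow-up assessments section and the Adverse event monitoring section so that capture comes before any judgement of cause:

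1. Record all SAEs in both arms, whatever the suspected cause.
2. At week 4, month 3 and month 6, ask both arms the same questions about the events already listed as expected, plus falls or syncope.
3. Have the clinical lead assess relatedness afterwards. If a restriction to related events is wanted, apply it to expedited reporting only.
4. Cross-check SAEs against admissions in the health resource use questionnaire at months 3 and 6.
5. Tabulate events by arm with risk differences and 95% CIs, described as descriptive.

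The cost is one added block in the existing questionnaires and some extra SAE processing, with no new assessments. Comparisons of rare SAEs will stay imprecise (about 20% to 28% power for an assumed 2% against 4% with 271 per arm). The gain is a safety record not selected by presumed cause, rather than a formal test.
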